#### Secondary Outcomes

##### Insomnia Severity Index (ISI)

The ISI is a validated patient-reported outcome of insomnia designed to specifically assess the impact of insomnia on daytime functioning and the severity of associated distress (34). The ISI includes seven items that are scored on a five-point scale ranging from 0 to 4 with higher scores representing more severe insomnia symptoms. The optimal cutoff scores are 0-7 (no clinically significant sleep difficulties), 8-14 (sleep difficulties warrant further investigation), and 15+ (presence of clinically significant insomnia). The ISI has demonstrated internal consistency, reliability, construct validity, specificity, and sensitivity (34). Participants who report a ≥8 reduction in ISI score or achieve an ISI score <8 after treatment are considered insomnia responders (35, 36).

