### Study Design

This study is a randomized controlled trial conducted at the Chengdu University of Traditional Chinese Medicine and the Geriatric Hospital of Sichuan Province, Chengdu, China. A total of 64 patients with essential hypertension and 10 healthy subjects will be recruited. 64 patients will be randomly allocated in a 1:1 ratio to either the acupuncture or sham acupuncture group. Patients will receive 10 treatments over 4 weeks. The primary outcome is the 24-h average blood pressure measured with 24-h blood pressure monitoring (24-h ABPM) at 4 weeks. Secondary outcomes include blood pressure measured at 8 weeks, the 24-h circadian rhythm of blood pressure, the sleep quality measured by the Insomnia Severity Index (ISI), cognitive function measured by the Montreal Cognitive Assessment (MoCA), TCMBC, health-related quality of life, patient's treatment expectancy, and adverse events. The details of the study design are shown in Figure 1. The timeline of recruitment, interventions, and outcome measurements is shown in Table 1.

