#### Eligibility Criteria

##### Hypertension Patients

###### Diagnostic Criteria.

The patient will be diagnosed with essential hypertension according to the 2017 ACC/AHA Clinical Practice Guidelines (16).

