###### Inclusion Criteria.

(1) Between 18 to 60 years old, (2) free from any kind of drugs at least 2 weeks before inclusion, (3) naivety to acupuncture treatment for hypertension, and (4) willingness to participate in this study and provide written conformed consents.

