###### Exclusion Criteria.

(1) With serious primary diseases such as cardiovascular, cerebrovascular, kidney and hematopoietic system, or metabolic diseases such as diabetes and thyroid dysfunction; (2) with skin diseases and skin damage on the skin or acupoints of the test site; (3) women with pregnancy or lactation or have pregnancy plans in the past year; (4) with history of epilepsy and obstructive sleep apnea syndrome; (5) with history of severe mental disorders or psychoactive substance dependence; (6) with abnormality in a laboratory test of blood biochemistry or with contagious risks; (7) used to suffer from acute diseases in recent 2 weeks, such as high gastritis or fever; (8) once received acupuncture treatment; (9) participating in other clinical trials.

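### The ISI responder rule has no baseline condition, so participants who start and stay below 8 count as insomnia responders, even if unchanged or worse within 0-7

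*Protocol article*

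**What the plan says.** The ISI section of the protocol article describes the scale ("The ISI includes seven items that are scored on a five-point scale ranging from 0 to 4 with higher scores representing more severe insomnia symptoms"), so the total runs from 0 to 28. It gives the lowest band as "0-7 (no clinically significant sleep difficulties", followed by 8-14 and 15 or more. It then defines response: "Participants who report a ≥8 reduction in ISI score or achieve an ISI score <8 after treatment are considered insomnia responders".

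The eligibility sections describe who enters. Under Diagnostic Criteria: "The patient will be diagnosed with essential hypertension according to the 2017 ACC/AHA Clinical Practice Guidelines". The Inclusion Criteria begin "Between 18 to 60 years old, (2) free from any kind of drugs at least 2 weeks before inclusion" and go on to acupuncture naivety and consent. The only sleep-related item under Exclusion Criteria is "with history of epilepsy and obstructive sleep apnea syndrome". None of these sections requires insomnia or a minimum ISI.

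Study Design lists among the secondary outcomes "the sleep quality measured by the Insomnia Severity Index (ISI", and the trial process chart (Table 1) collects the ISI at weeks 0, 4 and 8. The Statistical Analysis Plan section does not mention the ISI or a responder analysis.

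**The concern.** A rule that credits a final score below 8 makes sense when everyone starts at 8 or above, because reaching that band then requires improvement. This trial recruits for hypertension, so some participants may already be in that band at entry. For them the second limb of the rule is met by staying where they are, or by getting worse without leaving the band. A responder rate built this way mixes patients whose insomnia resolved with patients who had none. It would overstate how often insomnia responded in either arm and would tend to hide a real difference between the arms. Sleep is part of the second objective in the Introduction and is taken up again in the Discussion, so a reported responder rate is likely to be read as evidence.

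**Working it through.** **Step 1. What the rule does at each baseline.** Let b be the baseline and f the post-treatment ISI. A participant responds if b - f ≥ 8 or f < 8.

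- If b is 0 to 7, the largest possible fall is 7 - 0 = 7, so the first limb can never apply. Response then depends only on f < 8.
- There are 8 × 8 = 64 score pairs with both b and f in 0-7 (the match with the sample size is a coincidence). All 64 count as response: 28 are rises (such as 2 to 7), 8 are unchanged and 28 are falls.
- A participant who starts at 3 and ends at 9 is not a responder. Worsening is credited only while the final score stays at 7 or below.
- If b is 8 or more, no rise can qualify: f > b ≥ 8 fails both limbs. The fault is confined to participants with baseline ISI below 8.

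**Step 2. Effect on the reported rates.** The article states no expected responder rate, so there is no figure to reproduce. All inputs below are assumptions for illustration.

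- q: share with baseline ISI below 8, equal in both arms; range 30% to 70%.
- p1 = 40%, p0 = 20%: response among those with baseline ISI of 8 or more, acupuncture and sham.
- All participants with baseline ISI below 8 end below 8, so they respond at 100% in both arms.

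Reported rate = q + (1 - q)p. Reported difference = (1 - q)(p1 - p0).

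| q | Acupuncture | Sham | Difference |
|---|---|---|---|
| 0% | 40% | 20% | 20 points |
| 30% | 0.30 + 0.70 × 0.40 = 58% | 0.30 + 0.70 × 0.20 = 44% | 14 points |
| 50% | 0.50 + 0.50 × 0.40 = 70% | 0.50 + 0.50 × 0.20 = 60% | 10 points |
| 70% | 0.70 + 0.30 × 0.40 = 82% | 0.70 + 0.30 × 0.20 = 76% | 6 points |

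At q = 50%, 0.50/0.60 = 83% of the sham responders would have had a baseline ISI below 8.

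**Step 3. How far this depends on the last assumption.** Let r1 and r0 be the shares of low-baseline participants who end below 8 in each arm. The difference is then q(r1 - r0) + (1 - q)(p1 - p0). If r1 = r0, the factor 1 - q holds whatever their common value. With both at 90% and q = 50%, the rates are 0.45 + 0.20 = 65% and 0.45 + 0.10 = 55%, again 10 points apart. If r1 and r0 differ, the first term is no longer zero and the dilution is no longer exactly 1 - q. The rates are inflated whenever low-baseline participants meet the rule more often than the others do.

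**The case against.** The strongest reply is that the responder rule is not shown to be an endpoint at all. The named secondary outcome is the ISI itself. The responder sentence closes a description of the instrument, and no test or sample size rests on it. This stands, and it limits the reach of the point. A reader might infer that the sleep objective cannot be answered; the article does not support that, because the ISI score is collected at weeks 0, 4 and 8 and the rule leaves it untouched.

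A second reply is that the term insomnia responder, and the idea of achieving a score below 8, suggest people who started at 8 or above, and that a separate analysis plan may set the denominator. That is a fair reading of the intent. However, the subject of the sentence is participants in general, and the article defines no insomnia subset. The point is that the stated rule misclassifies patients if followed as written, whatever detail may be given elsewhere.

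A third reply is that the figures are illustrative. That also stands. The response rates, q and stability below 8 are all assumed. The Discussion calls insomnia common in these patients without giving a share; if q were near zero the problem would vanish. A reader might also infer that the arm difference must always shrink, or that any worsening patient counts as a responder. Steps 1 and 3 of the working show that neither holds without conditions.

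**Conclusion.** The point holds as a fault in a stated definition. That low-baseline participants are counted as responders when unchanged or worse within 0-7 follows from the rule and the entry criteria alone, with no outside figure. The size is uncertain. The factor of about 1 - q requires low-baseline participants to stay below 8 at about the same rate in both arms, and the loss from 20 points to 14, 10 or 6 further assumes true rates of 40% and 20% and q of 30%, 50% or 70%. The consequence is confined to the responder dichotomy of one secondary outcome. The primary blood pressure outcome, the sample size and the ISI score are not affected. It deserves correction before any responder rate is reported.

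**What to change.** Amend the responder sentence so that response is defined only among participants with baseline ISI of 8 or more, and state that this group is the denominator in each arm. Eight is the article's own boundary above its lowest band, and with this condition no one whose score rises can be a responder. The article also gives a band starting at 15, so the authors should say that they chose 8. A one-point change from 8 to 7 would still count as response, which is a reason to keep the dichotomy supportive. The main ISI analysis should be the score in all randomised patients, adjusted for baseline, as the article already does in its blood pressure model.

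This takes about one sentence and no new data, since the ISI is already measured at week 0. The cost is a smaller responder denominator. On a second set of assumptions (60% against 30% among those at 8 or more, half of each arm of 32 below 8 and all staying there, no dropout), power is about 27% for the all-patient rates of 80% and 65%, and about 40% in the 16 per arm who remain. On these assumptions the restriction loses no power, but the responder comparison stays exploratory.

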##### Montreal Cognitive Assessment (MoCA)

The MoCA is a rapid screening instrument to identify mild cognitive impairment. The validity and reliability of the MoCA have been demonstrated in previous studies (37, 38). MoCA includes eight cognitive domains to assess attention and concentration, executive functions, memory, language, visuoconstructional skills, conceptual thinking, calculations, and orientation (39). The total possible score is 30 points, and a score of ≥26 is considered a non-cognitive impairment. We will use the MoCA to monitor the effect of intervention on hypertension-related cognitive impairment.

##### The Short Form-12 Health Survey (SF-12)

The SF-12 is a generic and well-established health-related quality of life measure that has been commonly used in both general populations and various patient cohorts (40). The SF-12 contains 8 domains, including physical functioning; role-physical; bodily pain; general health; vitality; social functioning; role-emotional; and mental health (41). The SF-12 can be completed in 2 min. The SF-12 is used to evaluate the treatment effect in patients with hypertension (42).

##### Traditional Chinese Medicine Body Constitution (TCMBC)

TCMBC is a validated tool of patient categorization according to Chinese medicine diagnosis, which has been widely applied in practice by Chinese medicine practitioners (43). TCMBC has 60 items to measure the 9 types of patients: gentleness, Qi-deficiency, Yang-deficiency, Yin-deficiency, phlegm-wetness, wetness-heat, blood-stasis, Qi-depression, and special diathesis (44).

##### Patient's Treatment Expectancy

The Acupuncture Expectancy Scale (AES) is a 4-item instrument developed to measure outcome expectancy in the context of the acupuncture treatment (45). It has demonstrated reliability and validity in oncology populations with a Cronbach α of 0.95 and is sensitive to change over time in response to the acupuncture treatment (46). It has also been shown to correlate with patient self-efficacy and treatment satisfaction (45). The score ranges from 4 to 20, with higher scores indicating a greater patient expectation of improvement.

### Sample Collection and Preservation

We will collect fasting serum and urine samples before acupuncture treatment and on the second day of the final treatment from 8:00–9:00 a.m. We will also collect biospecimens from healthy subjects. Participants are required to (1) be free from the intake of alcohol, refresher drinks, coffee, amino acids, hormone, and vitamin supplements 48 h before sampling, (2) and maintain a regular diet and sleep habits, (3) avoid strenuous exercise 24 h before sampling; and (4) be fasting for 12 h before sampling. Fasting blood samples will be collected into vacutainer tubes with a coagulant; meanwhile, urine samples will be collected in a urinal cup. Both blood and urine samples will be immediately cooled to 4°C. Then these samples will be centrifuged within 2 h at 1500 rpm for 15 min. When completed, serum and urine samples will be separated and transferred to new vials. These samples will be finally stored frozen (−80°C) until metabolomic analysis preparation.

### Metabolomics Analysis

Serum samples will be pre-processed, divided for the available targeted and non-targeted metabolomics methods, and dried. Samples will then be reconstituted and analyzed using metabolomic platforms. The preliminary targeted analysis will consist of mining for metabolites in the Krebs Cycle and others identified in previous studies (23–25). Secondary analysis will leverage non-targeted (differential features analysis) workflows of the entire LC-MS/GC-MS datasets through a combination of the vendor, open source, and commercial software tools, followed by a metabolite identification pipeline to identify statistically important features.

### Safety Assessment

Patient safety will be monitored throughout the trial, with reporting of adverse events (AEs) and serious adverse events (SAEs), such as subcutaneous hemorrhage, vertigo, stroke, or even death. All AEs/SAEs will be recorded carefully and reported immediately in the case report form.

### Sample Size

According to preliminary data from our pilot study, acupuncture was associated with a 9.6-mmHg (δ) greater reduction of 24-h average systolic blood pressure and a 7.7-mmHg greater reduction of 24-h average diastolic blood pressure as compared with sham acupuncture. Conservatively, we hypothesized that acupuncture is associated with a 7.5 mmHg reduction (σ) in 24-h systolic blood pressure compared to sham acupuncture. The significance level was set at 0.05 (α = 0.05, *Z*_α_ = 1.96), and the power of the test was set at 0.9 (1-β = 0.9, *Z*_1−β_ = 1.28). A total of 64 participants will be required in this study (32 in each group), including compensation for an anticipated dropout rate of 20%. Additionally, 10 healthy participants will be recruited as the healthy control group.

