## Abstract

Essential hypertension is a polygenic cardiovascular disease that is associated with maladaptive metabolic changes. Acupuncture as a non-pharmacologic intervention is used to lower blood pressure and improve metabolic dysfunction. However, such effects have not been clinically characterized. We will conduct a randomized clinical trial to evaluate the antihypertensive effect of acupuncture among patients with essential hypertension and determine the associated metabolic improvements. This study is a phase II, two-arm, randomized, sham-controlled trial (Trial registration: ChiCTR2100043737), in which biospecimens will be collected for metabolic profiling. A total of 64 patients with a clinical diagnosis of essential hypertension will be randomly assigned to either the acupuncture or the sham acupuncture group in a 1:1 ratio. All participants will receive 10 treatments over 4 weeks, with three sessions per week for the first 2 weeks and two sessions per week for the remaining weeks. The primary outcome is the change of the systolic and diastolic blood pressure measured by the 24-h ambulatory blood pressure monitoring from baseline to 4 weeks. Secondary outcomes include the circadian rhythm of blood pressure, sleep quality measured by the Insomnia Severity Index, cognitive function measured by the Montreal Cognitive Assessment, and others. Fasting blood serum and urine samples will be collected at baseline and 4 weeks for targeted and untargeted metabolomics analysis. We will use the mixed-effects model and other related bioinformatics approaches to analyze the clinical and metabolome data. This metabolomic-based trial will provide important clinical data regarding the efficacy of acupuncture for essential hypertension to better inform evidence-based care delivery for hypertension patients. Moreover, the findings will offer important insights into the mechanism of action of acupuncture for hypertension by revealing its effect on metabolism. The results of this study will be used to inform the design of a statistically powered, multicenter, randomized trial. We will publish the study findings in peer-reviewed journals. The ethical approval of this study has been reviewed and approved by the Sichuan Regional Ethics Review Committee on Traditional Chinese Medicine (ID: 2021KL-006). The outcomes of the trial will be disseminated through peer-reviewed publications.

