### Statistical Analysis Plan

Clinical data will be analyzed with SPSS 24.0 software (SPSS Inc, Chicago, IL, USA). Continuous variables will be presented as mean and SD or as median and interquartile if they are not normally distributed. The baseline variables will be analyzed by the independent-samples t-test and Mann–Whitney U test, where appropriate. Categorical data will be presented as percentages. We will use the mixed-effects model to compare the effect of acupuncture vs. sham acupuncture on blood pressure from baseline to 4 and 8 weeks. The fixed effects are treatment arm, time, group^*^time interaction, and baseline outcome. For metabolomics data, the multivariate and univariate analysis will be performed in combination to determine the plasma metabolites that distinguish EH patients from a healthy subjects, and metabolites that exhibit significant changes before and after treatment in each treatment arm. We will use the Partial least square discriminant analysis (PLS-DA) in SIMCA-P (version 14.0; Umetrics, Umeå, Sweden) and the MetaboAnalyst (http://www.metaboanalyst.ca/MetaboAnalyst/) to fulfill the identification of differential metabolites between groups. All statistical tests will be two-sided, and statistical significance will be set at 5%.

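### The Sample Size section tags 7.5 mmHg both as a treatment difference and as σ, and no standard per-arm calculation on its figures gives 32 per arm at 90% power

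*Protocol article*

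**What the plan says.** The Sample Size section starts from pilot data in which "acupuncture was associated with a 9.6-mmHg (δ) greater reduction of 24-h average systolic blood pressure", together with "a 7.7-mmHg greater reduction of 24-h average diastolic blood pressure as compared with sham acupuncture". The planning assumption follows: "Conservatively, we hypothesized that acupuncture is associated with a 7.5 mmHg reduction (σ) in 24-h systolic blood pressure compared to sham acupuncture".

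The error rates are fixed in the same paragraph: "The significance level was set at 0.05" (with a z-value of 1.96) and "the power of the test was set at 0.9" (with a z-value of 1.28). The Statistical Analysis Plan section agrees on sidedness: "All statistical tests will be two-sided, and statistical significance will be set at 5" per cent.

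The result is given as "A total of 64 participants will be required in this study (32 in each group), including compensation for an anticipated dropout rate of 20" per cent. Allocation is 1:1. The section gives no formula and calls no quantity a standard deviation.

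**The concern.** In a two-mean calculation δ is the difference to be detected and σ is the SD of the outcome. Here both symbols sit on between-group differences: δ on the one seen in the pilot, σ on the one hypothesised for this trial. The word for caution in front of 7.5 makes sense only if 7.5 is a difference smaller than 9.6. As an SD it would have nothing to be cautious against.

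The paragraph gives alpha, power, both z-values, δ, σ, dropout and N, so it presents a complete calculation that a reader should be able to repeat. If it cannot be repeated, the 90% power for the primary systolic endpoint is an unverified claim. A reader of the eventual result, particularly a null one, would then not know what size of effect the trial could have detected.

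**Working it through.** **Inputs from the Sample Size section.** z = 1.96 and 1.28 (sum 3.24); 9.6 mmHg tagged δ; 7.5 mmHg tagged σ; dropout 20%; stated result 32 per arm.

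**Formula.** Evaluable n per arm = 2 × 3.24² × σ²/δ². Randomised n per arm = n/0.8.

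**Attempt to reproduce 32 per arm**

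| Reading | Evaluable per arm | Randomised per arm |
|---|---|---|
| As printed: δ = 9.6, σ = 7.5 | 2 × 10.4976 × 56.25/92.16 = 12.8, so 13 | 17 |
| Exchanged: δ = 7.5, σ = 9.6 | 2 × 10.4976 × 92.16/56.25 = 34.4, so 35 | 34.4/0.8 = 43.0; 35/0.8 = 43.75, so 44 |
| 7.5 as both | 2 × 10.4976 = 21.0, so 21 | 27 |

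With unrounded z-values the last row becomes 22 and 28. Multiplying by 1.2 instead of dividing by 0.8 gives 13 × 1.2 = 15.6 (16), 35 × 1.2 = 42 and 21 × 1.2 = 25.2 (26). Pairings that bring in the diastolic 7.7 mmHg, at two-sided 5% and 90% power, give 18, 25, 29 and 42 per arm. None is 32.

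**Where 32 does arise.** With the symbols as printed, the total over both arms is 4 × 10.4976 × 56.25/92.16 = 25.63, and 25.63/0.8 = 32.04. Rounding first gives 26 × 1.2 = 31.2, so 32. This looks like a two-arm total taken as a per-arm figure and doubled to 64. The same 25.63 is a per-arm number if the variance of the change score is set to 2σ² (no correlation between baseline and week 4), which the section does not say. Both routes use 9.6 as the effect, not the hypothesised 7.5.

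**Power with the stated N.** 32 × 0.8 = 25.6 evaluable per arm. Two-sample t-test, two-sided 5%, at 25 and 26 per arm:

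- as printed (9.6 over 7.5): 99.3% and 99.5%
- 7.5 as both: 93.4% and 94.2%
- exchanged (7.5 over 9.6): 77.2% and 78.9%

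**SD needed for 90% power if 7.5 is the difference.** Normal approximation: σ = 7.5 × √(n/2)/3.24, which is 8.18 at n = 25, 8.28 at 25.6, 8.35 at 26 and 8.45 at 26.67 (32/1.2). The t-test version gives 8.0 to 8.3 over the same range. No such SD is stated.

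**Sensitivity to the SD.** The SDs below are assumptions, since the document gives none. The difference detectable with 90% power is 7.5 × SD/8.01 at n = 25 and 7.5 × SD/8.18 at n = 26, where 8.01 and 8.18 are the t-based SDs that give 90% power at 7.5 mmHg.

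| Assumed SD (mmHg) | Power at 7.5 mmHg, 25–26 per arm | Detectable with 90% power (mmHg) |
|---|---|---|
| 7 | 96–97% | 6.4–6.6 |
| 8 | 90–91% | 7.3–7.5 |
| 9 | 82–84% | 8.3–8.4 |
| 10 | 74–76% | 9.2–9.4 |
| 12 | 58–60% | 11.0–11.2 |

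**The case against.** - **32 is not unreachable.** A reader might infer that the number has no source in the paragraph at all. That goes too far: the printed symbols lead to 32 as a two-arm total, or per arm with a doubled variance. This stands, and it limits the point to standard per-arm calculations. It does not rescue the stated figure. The first route is itself a slip, and the second rests on an unstated variance and sets aside the hypothesised 7.5.
- **Underpowering is not shown.** A reader might conclude that the trial is too small. The document does not support that. Taken literally, the symbols give about 99% power, and power falls below 90% only if 7.5 is the difference and the SD exceeds roughly 8 mmHg. The t-test figures also ignore the planned mixed model with baseline as a fixed effect. If 9.6 were the SD of the week-4 value and its correlation with baseline were 0.5 (an assumption), the residual SD would be 9.6 × √0.75 = 8.3 and power at 26 per arm about 89%.
- **A condensed article may leave the SD to the full protocol.** Agreed, so the absent SD alone is not the finding. The finding is that the σ the article does print sits on a treatment difference, and that the N it prints does not follow.
- **The Abstract might seem to concede low power** when it says "The results of this study will be used to inform the design of a statistically powered, multicenter, randomized trial". A phase II trial can be powered for 24-h systolic pressure and still precede a larger one, so this is no contradiction and adds nothing to the point.

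**Conclusion.** The paragraph is wrong as written. One figure serves as both the hypothesised difference and σ, and the stated 32 per arm at two-sided 5%, 90% power and 20% dropout is not reproduced by any standard per-arm two-sample calculation on its figures (17, 43–44 or 27). The likeliest source of 32 is a two-arm total under the printed symbols, but the document does not confirm this.

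With 25 to 26 evaluable per arm, power lies between about 77% and 99% depending on which reading is meant, so the 90% claim is unsupported in an unknown direction. These figures assume an unadjusted comparison of two means with equal SDs and exactly the anticipated dropout. The endpoint, allocation and planned analysis are not affected.

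**What to change.** Rewrite the Sample Size paragraph so that it:

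1. states which figure is the assumed between-group difference and which is the SD. The SD should be that of the change in 24-h systolic pressure, or the baseline-adjusted residual SD to match the planned model, with its source. The authors must settle this from their own calculation; the text alone does not show whether 7.5 or 9.6 was used as the difference;
2. gives the formula, including the variance used for the change score;
3. says whether 32 was a total or a per-arm figure.

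Keep N = 64, and restate the power, or the difference detectable with 90% power, for 25 to 26 evaluable per arm over SDs on both sides of 8 mmHg, as in the sensitivity table above.

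The cost is a text change with no extra patients. The restated power may be less favourable than 90%.
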